### Facilitator training

The HDHK program targets male facilitators with relevant discipline knowledge and experience. Although experienced physical education (PE) teachers are not specifically targeted, they are ideally suited to deliver the program. PE teachers have experience in teaching children, qualifications in education, expertise in health-related areas, and access to and understanding of schools. Importantly, they have the distinct skills and expertise to safely and effectively run the practical sessions. The training workshops are 6-8 hours of face-to-face contact and are designed to cover the background information to the program, session-by-session content knowledge, and the mechanics of the program (leading group sessions, role play, using the facilitator manual, homework activities, responses to common questions/problems and evaluation procedures).

A network of trained facilitators will be established to deliver the program in their local areas. Two facilitators will be paid to deliver the program. The lead facilitator's role is to present all materials and lead the delivery of the sessions. The co-facilitator provides a supporting role for the lead during all sessions (including equipment management, assisting in concept explanations and management of group-based activities), administrative support prior to (participant weigh-in, attendance sheets and homework compliance) and post (participant feedback questionnaires) all sessions. Both facilitators are responsible for completing the facilitator session feedback (independently) and for liaising with each other regarding equipment and resource requirements for each session.

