*Dose delivered*	To what extent were all intervention components implemented?	Facilitators HDHK research staff	* Independent self-reported checklist from Lead and Co Facilitator regarding the amount of pre-prepared content delivered and any non-delivered content (theoretical and practical) * Observation checklist of delivered content from independent observer to validate facilitator self-report checklist	* At the conclusion of each session (Checklists will be faxed to research staff post-delivery) * At least two observations per seven session program	* Calculated score based on percentage of intended content included * Percentage difference score of researcher versus facilitator average of intended content included	* Formative - informal feedback to staff prior to the next intervention session * Summative - reported after the program is complete

*Dose received*	How did participants react to the activities presented during the intervention?	Participants	* Participant evaluation of each of the attended sessions (enjoyment, amount learnt, ease of understanding content, relevance to self, likelihood of strategy use, likes and suggested changes) * Post-program evaluation (likes, dislikes, comments, attitudes before, attitudes after, program activities, facilitators, resources)	* Post-session * Post-program	* Quantitative analysis of session scores; Qualitative analysis of likes and suggestion themes per session and across the program	* Summative - reported after the program is complete

	To what extent did participants engage in recommended follow-up behavior?	Participants	* Father's log book and green slip homework activities; Kid's log book	* Father's log book (post-program); Kids log book (during and post program); Father's green slip homework (weekly)	* Level of follow-up activity completed included as a factor during quantitative analysis	* Summative - reported after the program is complete

*Reach*	What proportion of fathers attended greater than 70% of sessions (5 of 7)?	Facilitators	* Session roll for attendance	* Recorded at each session	* Level of attendance included as a mediator during quantitative analysis	* Summative - reported after the program is complete

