### Community Program Feasibility

The feasibility of the program as a community intervention will also be evaluated using a number of metrics including recruitment (achievement of target sample size), attendance (at program sessions), retention (retention rates at 6-month follow-up) and participant perceptions collected from fathers about program satisfaction via a questionnaire (end of program evaluation) that focuses on: open ended feedback of positives and negatives of the program; multiple choice questions regarding prior weight-loss experiences and reasons for joining the program; and Likert scale (5-point) questions anchored from (1) strongly disagree to (5) strongly agree regarding perceptions of program content, program structure, quality of facilitators, quality of program resources, and perceived changes made during the program. Additional information regarding the long term feasibility of the program will be obtained using a semi-structured post program phone interview and a long term process evaluation questionnaire (12 month post program evaluation).

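### A co-facilitator who helps deliver each session also handles the fathers' feedback forms on it, which exposes the session ratings in dose received to favorable-response bias of unknown size

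*Protocol article*

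**What the plan says.** The Facilitator training section of the protocol article describes two roles. The lead presents the material. Of the other it says: "The co-facilitator provides a supporting role for the lead during all sessions", a role that includes helping to explain concepts and manage group activities. The co-facilitator also provides "administrative support prior to (participant weigh-in, attendance sheets and homework compliance) and post (participant feedback questionnaires) all sessions". On payment the section states: "Two facilitators will be paid to deliver the program". Facilitators work in their own local areas.

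Table 4 (Process evaluation) lists three kinds of source under dose received:

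- a form after each session: "Participant evaluation of each of the attended sessions (enjoyment, amount learnt, ease of understanding content, relevance to self, likelihood of strategy use, likes and suggested" (the list ends with what fathers would alter), with quantitative analysis of the session scores and qualitative analysis of likes and suggestions;
- a form after the program: "Post-program evaluation (likes, dislikes, comments, attitudes before, attitudes after, program activities, facilitators, resources");
- for follow-up behavior: "Father's log book and green slip homework activities; Kid's log book".

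The Community Program Feasibility section describes an end-of-program satisfaction questionnaire with 5-point items on "perceptions of program content, program structure, quality of facilitators, quality of program resources" and perceived changes. It does not say who hands it out or collects it.

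Under the Stage 3 design, the program is modified in the light of outcome and process evaluation from the RCT and from each later run in 2011.

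**The concern.** A person who helps to deliver a session is not a neutral recipient of opinions about it. Fathers in a group of the planned size (15-20 per area in the community trial) know the co-facilitator and expect to see him again, so some may soften criticism on a form that passes through his hands.

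What is at stake is modest. The session scores are meant to show how fathers reacted to each session, and they help decide what is changed before the next run. If criticism is held back, the revisions draw on less information than they could. The article itself names poor monitoring of program integrity and of the dose received as a weakness of earlier obesity prevention programs, so the quality of this measure matters to its own aims.

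**Working it through.** The article states no figure for session ratings or satisfaction, so there is nothing to reproduce. The check is a reading of the sections against each other.

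**1. Is the role stated or only inferred?** It is stated. Facilitator training places the participant questionnaires in the co-facilitator's post-session duties, for all sessions, and has the same person supporting delivery of all sessions. The wording is administrative support. That covers at least handing out or collecting forms; it does not say that he reads or scores them.

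**2. How often does he meet the raters again?** The program has seven sessions. For 7 − 1 = 6 of them, the fathers who have just completed a form return to the same facilitators.

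**3. Which measures pass through this route?**

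| Measure | Source in the article | Handled by the co-facilitator? |
|---|---|---|
| Session ratings (dose received) | Form after each session, Table 4 | Yes, stated |
| Post-program evaluation (dose received) | Separate form, Table 4 | Not stated |
| Satisfaction, including facilitator quality | End-of-program questionnaire, Community Program Feasibility | Not stated |
| Follow-up behavior (dose received) | Log books and homework slips, Table 4 | Not a feedback form |
| Fathers' weight at 6 months (primary outcome) | Digital scale, Primary outcome measure | Not a feedback form |

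Only the first row is exposed on the article's own words.

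**4. Is there a check on these ratings?** For fidelity and dose delivered, Table 4 adds an independent observer at two or more of the seven sessions to validate the facilitators' checklists. The observer records content delivered, not what fathers thought of it. No comparable check is stated for the session ratings.

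**5. What can be said about size?** Write the observed mean rating of session *j* as *R_j* = *T_j* + *b_j*, where *T_j* is the mean under independent collection and *b_j* the courtesy shift. The article gives none of these quantities.

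- If *b_j* = *b* for every session, then *R_j* − *R_k* = *T_j* − *T_k*. The level is too high by *b*, but the contrast between sessions is intact.
- Contrasts are distorted only if *b_j* differs between sessions (for example, more courtesy after a poor one) or if answers pile up at the top of the scale. The article gives no scale for the session form, so neither can be assessed.

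**6. Where do the ratings go?** Table 4 reports dose received summatively, after a program ends. The ratings can therefore inform the next run, alongside outcome data and the other process elements.

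**The case against.** The strongest reply is that this is a condensed article. Anonymity and the return of forms belong in the facilitator manual, and facilitator training is said to cover evaluation procedures. That stands as far as it goes: silence on those details is not an error, and the manual may already provide for sealed forms. It does not remove the role assignment, which the article states.

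A second reply is that weak sessions can be found in other ways: checklists from both facilitators, the independent observer, the session 6 focus group on barriers, open-ended questions at the end of the program, a phone interview and a 12-month questionnaire. This also stands, and it is why the ratings count as one input among several. Some of these sources record content delivered, and the others come late in the program or after it. None replaces fathers' reactions to each session at the time.

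A reader might go further and infer that satisfaction scores and ratings of the facilitators are inflated because the facilitators collect them. The documents do not support that. Those items sit on the end-of-program questionnaire, whose handling is not described, and none of the listed session-form items names a facilitator. Nor do session ratings appear among the feasibility metrics, and no comparison between facilitators is planned that could be blunted.

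**Conclusion.** The point holds in a limited form. A stated allocation of duties exposes the session-rating part of dose received to favorable-response bias. The likely direction is upward, on the assumption that fathers are reluctant to criticize someone they know and will meet again; the article offers no evidence on direction or size. It would be wrong to say that the ratings are biased upward as a fact, or that differences between sessions will be hidden, since a common shift leaves those differences unchanged.

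The consequence is confined to the process evaluation and, through it, to one of several inputs to program modification. The primary outcome, the RCT comparison, and the log-book and homework part of dose received are unaffected. This is a cheap improvement, not a flaw that threatens the trial's conclusions.

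**What to change.** Have fathers place each session form, carrying a code and the session number but no name, in an envelope that they seal and that goes unopened to the research team. The trial already has such a route: under Physical activity (objective measure), pedometers and record sheets go back to the team in a prepaid envelope. The research team should hold the key to the codes. Session number on the form preserves the planned analysis by session and across the program.

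Return the end-of-program questionnaire by the same route, because it does rate the facilitators and its handling is not stated. If the facilitator manual already provides for this, a sentence saying so is enough.

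The cost is envelopes and one line in the manual. The downside is that a few more forms may go unreturned, so the number returned should be reported against attendance at each session.

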### Measures

A variety of data collection methods will be used to assess program impact, implementation, participation and fidelity. For the community RCT, participants will be blinded to group allocation at baseline assessment. Baseline assessments will be made 1-2 weeks before program commencement. Assessors will be trained by the same experienced researcher, and for anthropometric measurements, the protocols used are those prescribed by the International Society for the Advancement of Kinanthropometry [29]. A summary and brief description of the measures used for both the RCT and community trial programs is described in Table 3 with more specific details provided below.

**Table 3 T3:** Overview of HDHK RCT and community trial measures

Measure	RCT	Community trial
PHYSICAL MEASURES		
Weight	**Father & child(ren)**: Digital scale	**Father & child(ren)**: Digital scale
Height	**Father & child(ren)**: Portable stadiometer	**Father & child(ren)**: Portable stadiometer
BMI	**Father: **(kg/m^2^). **Child(ren): **(kg/m^2^) and z-scores.	**Father: **(kg/m^2^). **Child(ren): **(kg/m^2^) and z-scores.
Waist circumference	**Father**: 1) level with the umbilicus and 2) the widest point. **Child(ren)**: 1) level with the umbilicus and 2) the narrowest point + z-scores.	**Father**: 1) level with the umbilicus and 2) the greatest circumference point. **Child(ren)**: 1) level with the umbilicus and 2) the narrowest point + z-scores.
Blood Pressure and Resting Heart Rate	**Father & child(ren)**: Digital electronic monitor.	Not measured

PHYSICAL ACTIVITY AND SEDENTARY BEHAVIOR		
Physical activity (PA)	**Father & child(ren)**: Yamax200 pedometers for 7 consecutive days.	**Father**: Modified version of the Godin Leisure-Time Exercise Questionnaire (GLTEQ) [39]. **Eldest child **(Father proxy): Children's Leisure Activities Study Survey (CLASS) questionnaire [41].
Sedentary Behaviors	**Father**: Modified Sitting Questionnaire [42,43]. **Eldest child**: (Mother proxy) modified (CLASS) [41]	**Father**: Modified Sitting Questionnaire [42,43]. **Eldest child **(Father proxy): Indoor based activities section of CLASS [41].

NUTRITION AND DIETARY BEHAVIORS		
Dietary intake	**Father**: Australian Eating Survey (AES) [44]. **Eldest child **(Mother proxy): Australian Child and Adolescent Eating Survey (ACAES) [46].	**Father**: Modified AES relating to 8 key nutritional messages **Eldest child **(Father proxy): Modified AES relating to 8 key nutritional messages.
Portion size	Not measured.	**Father: **Photographs from the Dietary Questionnaire for Epidemiological Studies Version 2 [49].
Alcohol Consumption	Not measured	**Father**: Modified Alcohol Use Disorders Identification Test 2009 [52].
Parenting strategies for eating & PA	**Father and mother **(about eldest child): Parenting Strategies for Eating and Activity Scale (PEAS) [56].	**Father **(about eldest child): PEAS [56].
Child Feeding Habits	**Mother **(about eldest child): Child Feeding Questionnaire [55].	Not measured

PARENTING STRATEGIES		
Parenting for PA & nutrition	**Father **(about eldest child): A combination of parenting measures from previously validated sources with some new items	**Father **(about eldest child): A combination of parenting measures from previously validated sources with some new items
Parental engagement	**Father **(about eldest child): Parental Engagement Questionnaire [63,64] and additional questions on father's physical play	**Father **(about eldest child): Modified Parental Engagement Questionnaire (also questions relating to the father's perceptions of father's physical play with their eldest child).
Attitudes to rough and tumble play	Not measured.	**Father**: Semi structured interview

ADDITIONAL INFORMATION		
Socio-demographic information	**Father & child(ren)**: Age and socioeconomic status	**Father & child(ren)**: Age and socioeconomic status

#### Demographic characteristics

Background details and socio-demographic variables will be collected by questionnaire including age, marital status, occupation, gross annual family income, educational level, ethnic origin, language spoke at home, socioeconomic status (SES) and postcode. SES is based on postal code of residence using the Index of Relative Socioeconomic Advantage and Disadvantage from the Australian Bureau of Statistics census-based Socio-Economic Indexes for Areas (SEIFA) [30].

#### Primary outcome measure

The primary outcome measure is body weight of the fathers at 6-month follow-up. Weight will be measured with fathers wearing light clothing, without shoes on a digital scale to 0.1 kg (model CH-150 kp, A&D Mercury Pty Ltd, Australia). Weight will be recorded twice and the average of the two measures reported. The same protocol will be followed to record children's weight.

#### Secondary outcomes

##### BMI

will be calculated using the standard equation (weight [kg]/height[m]^2^). Height will be measured to 0.3 cm using the stretch stature method and a stadiometer (VR High Speed Counter) (Harpenden/Holtain, Mentone Education Centre, Morrabin, Victoria). Height will be recorded twice and the average of the two measures reported. For children, height and weight will be used to calculate BMI (kg/m^2^) and age- and sex-adjusted standardized scores (*z*-scores) based upon the UK reference data [31] and LMS methods [32] will be used. International Obesity Task Force cut points will be used to determine overweight or obesity [33].

##### Waist circumference

Waist circumference will be measured at two points for all participants. In fathers: (i) level with the umbilicus and (ii) at the greatest circumference between the lower costal border and the iliac crest; and in children: (i) level with the umbilicus and (ii) at the narrowest point. Each measurement will be recorded with a non-extensible steel tape (KDSF10-02, KDS Corporation, Osaka, Japan). Two measures will be taken and if the measures differ by more than one centimeter, a third will be recorded. The average of the measures will be reported and a waist *z*-score calculated for children [34].

##### Blood Pressure and Resting Heart Rate (RHR)

Systolic and diastolic blood pressures will be measured using a NISSEI/DS-105E digital electronic blood pressure monitor (Nihon Seimitsu Sokki Co. Ltd., Gunma, Japan) under standardized procedures. Participants will be seated for at least five minutes before blood pressure and RHR is recorded. Blood pressure and RHR will be measured three times and the average of the three measures will be reported.

##### Physical activity (objective measure)

Yamax SW700 pedometers (Yamax Corporation, Kumamoto City, Japan) will be used to objectively measure physical activity; they are considered to be more reliable than other brands of pedometers [35]. They have been validated in children [36] and adults [37]. Participants will be asked to wear pedometers for seven consecutive days and maintain their normal routine. At baseline assessments, participants will be instructed on how to attach the pedometers (at the waist on the right hand side) and asked to remove the pedometers only when sleeping, when the pedometer might get wet (e.g. swimming, showering) or during contact sports. At the end of the day, participants are instructed to record their steps and reset their pedometers to zero. Once seven days of monitoring has been completed, participants are instructed to place the pedometer and record sheet in the prepaid envelope provided and return to the research team. Participants will be included in all analyses if they have completed at least four weekdays of pedometer monitoring and one weekend day.

##### Physical activity (Father - questionnaire measure)

Self-reported physical activity will be collected using a modified version [38] of the validated Godin Leisure Time Exercise Questionnaire (GLTEQ) [39], that asked participants to report the average number of times per week, in the past month, they engaged in vigorous (rapid heartbeats, sweating), moderate (not exhausting, light perspiration) and mild (minimal effort and no perspiration) intensity physical activity, for a minimum of 10 minutes per session. As specified by the GLTEQ, weights of 9, 5 and 3 will be applied to vigorous, moderate and mild frequencies respectively and a summary score of the weighted physical activity per week will then be computed by adding vigorous, moderate and mild activity frequencies [39] to obtain an overall GLTEQ score. Participation responses for the moderate and vigorous activity categories will also be added to obtain total minutes of moderate and vigorous minutes per week. Physical activity measures will be converted into metabolic equivalent (MET) scores (i.e., MET-minutes/week) by multiplying reported weekly minutes in each intensity category by each respective MET-minute value (i.e., moderate intensity minutes multiplied by 4 MET and vigorous intensity by 7.5 MET) and mild intensity by 2.5 [40]. [For example, one hour (60 min) of moderate-intensity exercise would be equal to 240 MET-min of activity (60 minutes times 4 METs)].

##### Physical activity (Eldest child - questionnaire measure)

Assessed in the RCT by the mother using a modified Children's Leisure Activities Study Survey (CLASS), which has been validated in children 5 - 6 and 10 - 12 year of age [41]. In the community trial, fathers will complete a version of CLASS to obtain a measure of physical activity time for their children.

##### Sedentary behavior

For the eldest child in the RCT, the mother will complete a modified version of the CLASS, which has been validated in children 5 - 6 and 10 - 12 year of age [41]. In the community trial, fathers will complete a version of the CLASS to obtain a measure of time spent in various sedentary behaviors. Only questions relating to indoor leisure activities will be used (small screen recreation, homework, talking, reading, music and craft activities). To assess their sitting time, fathers will complete an adaptation of the Sitting Questionnaire, which has been shown to be both a valid and reliable measure of sitting time in various domains [42,43].

##### Dietary intake (Fathers)

will be assessed in the RCT using the Australian Eating Survey (AES). AES is a 120-item semi-quantitative Food Frequency Questionnaire (FFQ), used previously in Australian youth up to 16 years [44] and currently being validated in both adult males and females. Portion sizes for individual food items were generated by the Australian Bureau of Statistics (ABS) [45] and unpublished data from the 1995 Australian National Nutrition Survey; or the "natural" serving size for common items such as a slice of bread. Subjects are asked about frequency of their consumption over the previous six months with frequency options ranging from 'Never' up to '4 or more times per day' but varying depending on the food item. Twenty-one questions relate directly to the intake of vegetables and 11 questions relate to fruit. Seasonal availability of some fruits will be considered in the nutrient analysis. Nutrient intakes from the AES will be computed from the most current food composition database of Australian foods available, the Australian AusNut 1999 database (All Foods) Revision 17 and AusFoods (Brands) Revision 5 (Australian Government Publishing Service, Canberra) to generate individual mean daily macro-and micro-nutrient intakes. The AES includes questions about the total number of daily serves of fruit, vegetables, bread, dairy products, eggs, fat spreads, sweetened beverages and snack foods, as well as asking the type of bread, dairy products and fat spreads used. Twelve questions relate to food-related behaviors, including items on frequency of take-away food consumption and eating while watching television.

Dietary intake for fathers in the community trials will be assessed using a modified version of the AES. Eight questions related to the key nutritional messages of the program will be drawn from the full AES survey (milk type, fruit intake, vegetable intake, takeaway food intake, meals whilst watching television, sweetened drink intake, fruit juice intake, and snack frequency).

